### Study design

A single-center, randomized, parallel group, open label, non-inferiority study will be conducted to compare MPVC with CAU in MS patients (MonSter-1 study).

The intervention group will work with MSmonitor-Plus and Video calling Care (MPVC), the control group will receive CAU and maintain the number of outpatient consultations as applicable to the patient and will not use MPVC.

MS patients who do not participate in this study (e.g., because of a clear preference for the use of MVPC or for MSmonitor without video calling) will be asked to complete the baseline study questionnaires once. With this parallel study (MonSter-2 study), we can compare baseline characteristics in order to study the generalizability of the randomized controlled trial (RCT) outcomes.

Figure 1 presents the flow chart of the study. Tables 2 and 3 (assessment schedule) are schematic representations of the study design.

**Fig. 1 Fig1:**
[figure not shown]
Flow chart of the study

**Table 2 Tab2:** Schedule of assessments concerning patients and caregivers in the intervention arm

PROMs			Standard time points									Variable time points
			B	3 m	6 m	9 m	12 m	15 m	18 m	21 m	24 m	
**ID**	**PROMs by MSmonitor Plus, for MS patients, with or without a caregiver/partner**											
1a 1b	Actionable SF-Qualiveen	Screening questionnaire for bladder disorders.	X	X	X	X	X	X	X	X	X	
		In order to assess health-related quality of life of patients with urinary disorders in neurologic conditions	X	X	X	X	X	X	X	X	X	
2	Checklist	For individual tension strength	X	X	X	X	X	X	X	X	X	
3	MSIP	Multiple sclerosis impact profile	X	X	X	X	X	X	X	X	X	
4	MSIS-29	Multiple sclerosis impact scale 29	X	X	X	X	X	X	X	X	X	
5	NBD	Neurogenic bowel dysfunction score	X	X	X	X	X	X	X	X	X	
6	Quick Scan	Five questions about the impact of fatigue on daily life, the Modified Fatigue Impact Scale-5 item Version (MFIS-5) and eight questions about health-related quality of life, the Leeds MS Quality of Life (LMSQol) and the registration of medication use	X	X	X	X	X	X	X	X	X	Every day if needed
7	HADS	Hospital anxiety and depression scale. Consists of a depression scale and anxiety scale, both are determined by means of seven questions	X		X		X		X		X	
8	MSISQ-15	Questionnaire on intimacy and sexuality in multiple sclerosis (MS) or spinal cord injury	X		X		X		X		X	
9	MSQOL-54	MS-specific quality of life	X		X		X		X		X	
10	Natalizumab checklist	16 questions every 28 days, submitted 2 days prior to the infusion of natalizumab	X									Every 28 days, if needed
11	Do I have a schub	Consists of 4 questions that the patient must answer. This shows whether he/she should contact the doctor to check if they have a schub	X									Daily available
12	Diary	The patient can keep track of activities and moments of rest in order to gain insight into fatigue	X									Daily available
ID	**PROMs by eCRF, for patients, with or without a caregiver/partner**											
13	iMCQ	iMTA Medical Consumption Questionnaire	X	X	X	X	X	X	X	X	X	
14	iPCQ	iMTA Productivity Cost Questionnaire	X	X	X	X	X	X	X	X	X	
15	CFQ	Cognitive failure questionnaire	X		X		X		X		X	
16	EQ-5D-5L	Health questionnaire (Dutch version)	X		X		X		X		X	
17	IPA	Impact on participation and autonomy	X		X		X		X		X	
18	MSSES	MS Self Efficacy Scale	X		X		X		X		X	
19	PIH	Partners in Heath Scale	X		X		X		X		X	
	**PREMs by eCRF for patients, with or without a caregiver/partner**											
20	PTO	Patient satisfaction questionnaire Isala	X				X				X	
	**PROMs by eCRF for caregivers/partners of MS patients**											
21	CarerQol-7D/VAS	Quality of life of informal caregivers for use in economic evaluations	X		X		X		X		X	
15	CFQ	Cognitive failure questionnaire	X		X		X		X		X	
22	iVICQ	iMTA Valuation of Informal Care Questionnaire	X				X				X	

Data collection was performed using MS monitor and eCRF. PROMs and PREMs are ordered by 1) frequency of administration and 2) alphabet

*B* baseline, *m* month

*PROM* Patient-reported outcome measure, *PREM* Patient-Reported Experience Measure

**Table 3 Tab3:** Schedule of assessments concerning the control arm

ID	PROMs		Standard time points								
			B	3 m	6 m	9 m	12 m	15 m	18 m	21 m	24 m
	**PROMs by eCRF for MS patients, with or without a caregiver/partner**										
9	MSQOL-54	MS-specific quality of life	X		X		X		X		X
13	iMCQ	iMTA Medical Consumption Questionnaire	X	X	X	X	X	X	X	X	X
14	iPCQ	iMTA Productivity Cost Questionnaire	X	X	X	X	X	X	X	X	X
15	CFQ	Cognitive failure questionnaire	X		X		X		X		X
16	EQ-5D-5L	Health questionnaire (Dutch version)	X		X		X		X		X
17	IPA	Impact on participation and autonomy	X		X		X		X		X
18	MSSES	MS Self Efficacy Scale	X		X		X		X		X
19	PIH	Partners in Heath Scale	X		X		X		X		X
	**PREMs by eCRF for MS patients, with or without a caregiver/partner**										
20	PTO	Patient satisfaction questionnaire Isala	X				X				X
	**PROMs by eCRF for caregivers/partners of MS patients**										
22	iVICQ	Valuation of Informal Care Questionnaire	X				X				X
15	CFQ	Cognitive failure questionnaire	X		X		X		X		X
21	CarerQol	Quality of life	X		X		X		X		X

Data collection was performed using an eCRF

*B* baseline, *m* month

*PROM* Patient-reported outcome measure, *PREM* Patient-Reported Experience Measure

### Study population(s)

A total of 208 patients of all three types of MS, with or without their partner or informal caregiver will be included in the study (Tables 2 and 3). Most of the patients in the study have RRMS (relapses remitting, 80%), the least have PPMS (primary progressive, 8%) and the rest 10% SPMS (secondary progressive). This proportion corresponds to the prevalence of MS in the population of the Netherlands.

Inclusion criteria are 18 years of age or older, ability to understand Dutch and willingness and able to use MPVC.

Patients whose diagnosis of MS has not yet been clearly established or patients who have underlying diseases similar to MS in terms of symptoms (such as polyneuropathy, cerebral infarction, semi-lateral paralysis or other neurological diseases) will be excluded from participation.

The study team consists of the investigator, research nurse, the MS neurologist, and the MS nurse specialist.

### Setting

The study will be conducted at the MS Expertise Center of Isala Diaconessenhuis, Meppel location, Netherlands.

Isala is the largest general top clinical teaching hospital in the Netherlands with 6000 employees and 1100 beds. Isala is divided into 5 locations: Zwolle, Meppel, Steenwijk, Kampen and Heerde.

The study started in April 2021, followed by 1 year of inclusion and 2 years of follow-up. The last patient’s final study visit will be in 2024. The results should be finally analyzed in January 2025.

### Recruitment

Starting in April 2021, potential participants will be informed about the study during a consultation with one of the three MS neurologists, the nurse specialist or MS nurse. If patients are interested in participating in the study, their names will be placed on a trial list in our hospital’s Electronic Patient File (HIX). The coordinating investigator will contact the patient and explain the study. The coordinating investigator will ask if the participant has a partner/informal caregiver who would like to participate in the study. If the patient and eventual partner/informer caregiver agree, an Informed Consent Form (ICF) for the MS patient (ICF MS Patient) and – if applicable an ICF for the partner/informer caregiver (ICF partner/informer caregiver) - will be sent with a return envelope. The patient and partner/informal caregiver will be given 2 weeks to consider their decision to participate and if they have any questions, they can contact the investigator.

Upon receipt of the signed ICF, the coordinating investigator will sign the ICF and the patient and partner/informal caregiver will receive a copy. An appointment will be made for an inclusion session (by phone or face to face).

At baseline the patient and partner/informal caregiver will be registered in the electronic Case Report Form (eCRF) and will receive an email (the first) from the eCRF, immediately after enrollment with the initial invitation to fill out the research questionnaires.

Whether the research questionnaires were actually answered is tracked by the investigator. If research questionnaires are not completed on time, the patient and partner/informal caregiver will receive a reminder or are contacted by phone.

The intervention group will be signed up for the MSmonitor-Plus program and the nurse specialist will explain MPVC. A test appointment for a video calling connection via Beterdichtbij will also be made. Participants will receive an email from MSmonitor-Plus 4 times a year to complete questionnaires.

During standard MSmonitor-Plus appointments (every 3 months) the nurse specialist checks if the patient has completed the questionnaires. If the patient forgets to complete the questionnaires, the patient will be contacted by the nurse specialist (by phone or e-mail). The measurements and answers are recorded by the nurse specialist in the Electronic Patient Record.

### Sample size, concerning the effectiveness analysis

The sample size was based on detecting non-inferiority concerning the two subscales of the MSQol-54, i.e. the mental score and the physical score, at 2 years of follow-up.

We adopted the standard deviation (SD) of the baseline data of the Dutch MS Study [47] (largest SD, concerning preliminary data). The minimal clinically (non)important change (MIC) was estimate in accordance with a distribution-based approach.

Sample size calculation was performed using IBM SPSS SamplePower 3.0. Calculation with delta 8 points, SD 17.5, alpha 0.0125 (1-sided), and power 80% resulted in *n* = 93 required participants per arm. To compensate for 10% dropout, *n* = 104 participants per arm will be included in this study.

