### Statistical analyses

#### Clinical effectiveness analyses

Non-inferiority of MPVC compared to CAU, concerning both mental and physical scores of the MSQOL-54 at 2 years follow-up, will be analyzed using confidence intervals (1-tailed 98.75% or equivalently 2-tailed 97.5%).

When a confidence interval excludes the pre-defined non-inferiority margin of 8 points, non-inferiority will be concluded. In the case of substantial potential confounding (unbalanced baseline variables) however, analysis will be based on testing for non-inferiority to enable adjustment. If non-inferiority is demonstrated, superiority will be studied subsequently.

Courses of Proms between the two study arms will be compared using analyses for longitudinal data.

Analysis of primary outcomes will be performed in the per-protocol analysis set. Additional analyses will be performed in the (modified) intention-to-treat analysis set.

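### Alpha and the 80% power are set per score, but the objective names both MSQOL-54 scores and the decision rule does not say whether one or both must pass; if both must, joint power is about 66–76%

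*Protocol article*

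**What the plan says.** The sample size section of the protocol article names two primary scores: "The sample size was based on detecting non-inferiority concerning the two subscales of the MSQol-54, i.e. the mental score and the physical score". It then gives one calculation for both: "Calculation with delta 8 points, SD 17.5, alpha 0.0125 (1-sided), and power 80% resulted in" 93 per arm, raised to 104 for 10% dropout.

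The clinical effectiveness analyses section sets out the objective as "Non-inferiority of MPVC compared to CAU, concerning both mental and physical scores of the MSQOL-54 at 2 years follow-up". The interval level is "1-tailed 98.75% or equivalently 2-tailed 97.5" per cent, which matches one-sided 0.0125. The decision rule is: "When a confidence interval excludes the pre-defined non-inferiority margin of 8 points, non-inferiority will be concluded". Superiority is to be examined once non-inferiority has been shown; the section does not say on which score.

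The Methods paragraph of the abstract describes the primary outcome as physical and mental quality of life together, each to be equal or improved. No section says whether the trial's conclusion needs both scores or is drawn separately for each.

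**The concern.** The parts of the plan point to different designs. Splitting 0.025 into two halves of 0.0125 suits separate claims, or a claim that may rest on either score. Naming both scores in the objective suits a claim that needs both. The rule speaks of a single interval.

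Each design has a consequence that the protocol does not draw.

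- **Both scores required.** The power of the claim is the probability that both intervals clear the margin, which is below 80%. The alpha split then widens the intervals without adding any error control.
- **One score sufficient.** Non-inferiority on quality of life could be declared while the other summary score is worse by more than 8 points. That would not support an objective worded for physical and mental quality of life together.

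This is more than detail left to an analysis plan. The protocol itself fixes the alpha, the interval level, the margin and the wording of the conclusion, and these do not fit together.

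**Working it through.** **Inputs.** From the protocol article: margin 8 points, SD 17.5, one-sided alpha 0.0125, power 80%, 93 evaluable per arm, 1:1 allocation, two scores. Assumed, because the article does not give them: true difference 0 on both scores, the same SD on both, and a correlation ρ between the scores of 0 to 0.9.

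**Step 1: reproduce the stated size.** The normal approximation is n = 2 × [SD × (z₀.₉₈₇₅ + z₀.₈₀) / margin]² = 2 × [17.5 × (2.241 + 0.842) / 8]² = 90.97, so 91 per arm. With the noncentral t, 92 per arm gives 79.9% and 93 gives 80.4%, so 93 is reproduced exactly. Dropout: 93 / 0.90 = 103.3, so 104. The calculation has one margin and one SD, so its 80% is power for one score.

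**Step 2: power per score at 93 per arm.** SE = 17.5 × √(2/93) = 2.566, and 8 / 2.566 = 3.117.

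- At one-sided 0.0125: Φ(3.117 − 2.241) = 80.9% (80.4% by noncentral t).
- At one-sided 0.025: Φ(3.117 − 1.960) = 87.6% (87.3% by noncentral t).

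**Step 3: power for both, or for at least one.** Joint power is P(Z₁ ≤ q, Z₂ ≤ q) for a bivariate normal with correlation ρ, where Φ(q) is the normal-approximation power from step 2. At ρ = 0 this is the square: 0.8095² = 65.5% and 0.8764² = 76.8%. Power for at least one score is 2 × per-score power − joint power.

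| ρ | Both pass, 0.0125 each | Both pass, 0.025 each | At least one passes, 0.0125 each |
|---|---|---|---|
| 0 | 65.5% | 76.8% | 96.4% |
| 0.5 | 70.0% | 79.7% | 91.9% |
| 0.7 | 72.5% | 81.4% | 89.4% |
| 0.8 | 74.1% | 82.5% | 87.8% |
| 0.9 | 76.1% | 84.0% | 85.8% |

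Under a both-must-pass rule the split therefore costs between 84.0 − 76.1 = 7.9 and 76.8 − 65.5 = 11.3 percentage points of power.

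**Step 4: why no split is needed if both must pass.** A false joint claim requires that at least one score is truly beyond the margin, and that score must itself pass. The chance of this is at most the per-score alpha. Testing each score at one-sided 0.025 therefore keeps the joint error at or below 0.025.

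**Step 5: size for 80% joint power.** Evaluable patients per arm:

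| ρ | 0.025 each | 0.0125 each |
|---|---|---|
| 0 | 99 | 117 |
| 0.5 | 94 | 112 |
| 0.7 | 91 | 108 |
| 0.8 | 88 | 105 |
| 0.9 | 85 | 101 |

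At 0.025 per score, 93 per arm is close to enough unless the correlation is low. At 0.0125 it falls short across the whole range.

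**Step 6: the rule read literally, with one score sufficient.** If one score truly does not differ, its interval clears the margin about 80% of the time, however far the other score has fallen.

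**The case against.** The strongest reply is that the protocol nowhere states that both scores must pass. Saying that both are analysed is not a rule for combining them. The split alpha, the matching interval level and the singular interval in "When a confidence interval excludes the pre-defined non-inferiority margin of 8 points" fit a coherent design with a separate test and a separate conclusion for each score. In that design the split is needed, family-wise error is held at 0.025, and 80% per score is the proper target. This stands. A reader might infer that the stated 80% is simply wrong and that alpha is being wasted. The document does not support that, because both statements hold only if the claim is joint.

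Two further inferences should not be drawn. The rule gives no sign for the margin, but the direction is clear from a one-tailed interval for non-inferiority of MPVC against CAU and a goal of equal or improved quality of life. Nor does the protocol say that superiority on either score would suffice; it says only that superiority will be studied afterwards.

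The size of the shortfall also depends on assumptions. The article gives no correlation, and it describes 17.5 as the largest SD, so a smaller SD on one score would raise joint power. Finally, 0.0125 per score under a joint rule is conservative: it costs power but does not raise the false-positive rate.

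The reply does not remove the defect. The per-score design is consistent only if each conclusion is confined to its own score. The rule does not say so, and the objective is worded for both.

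**Conclusion.** The concern holds in conditional form: the decision rule is badly fixed. Alpha and power are set per score, the objective is worded for both scores, and the rule taken literally lets one score carry the conclusion.

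If both scores are required, the power at 93 per arm and one-sided 0.0125 is about 66% to 76% for correlations from 0 to 0.9, against the 80% stated. This assumes a true difference of 0 and SD 17.5 on both scores. If separate claims are intended, 0.0125 and 80% per score stand as written, and what is missing is the restriction of each conclusion to its own score. The document does not settle which design was meant, so an unconditional statement that the power is wrong would go too far.

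**What to change.** State one rule before the final analysis, which the protocol plans for January 2025.

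- **Preferred, matching the objective as worded.** Conclude overall non-inferiority on quality of life only if the lower confidence limit for MPVC minus CAU lies above −8 points on both summary scores, and restate the power as joint. One-sided 0.025 per score (two-sided 95% intervals) may then be used, giving about 87% per score and 77–84% jointly with the same 93 evaluable per arm. Keeping 0.0125 is also valid but conservative, with joint power of 66–76%.
- **If separate claims are intended.** Keep 0.0125, label the 80% as per score, confine each conclusion to its own score, and make no overall non-inferiority claim from one score alone.

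Either way, say on which score or scores non-inferiority must hold before superiority is examined.

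The cost is a change of wording and a restated power figure that may look less favourable; no extra patients are needed. All 208 patients were already enrolled by the end of May 2022 and the trial is open label. A change of alpha therefore needs a documented and justified amendment made before the data are analysed. Choosing the rule after seeing the results would undermine the conclusion.

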### Randomization

Stratified block randomization will be performed using the randomization module of our eCRF, ResearchManager (ResearchManager, Deventer, The Netherlands). ResearchManager is certified with ISO 27001 and NEN7510 and is affiliated with the 21 CFR part 11 FDA, which describes the administration of electronic records in a quality medical system of a medical device company.

Two strata will be used, i.e. sex and type of MS (RRMS, SPMS and PPMS). Distributions will be based on the known distributions in the Netherlands.

### Care as usual (CAU)

All patients in both study group receive care as usual. Care as usual consists first of making the correct diagnosis of MS (MRI scan, blood test and possibly lumbar puncture) and initiating the correct treatment method, adapted to the patient. MS care usually starts with DMT. Nearly all disease-modulating agents for MS are associated with suppression of the immune system that makes people with MS more susceptible to infections including viral infections. A tailor-made monitoring program (different per DMT) therefore applies to all these DMTs to control these risks as much as possible.

After starting a DMT, clinical and radiological monitoring should take place according to DMT-specific guidelines: In the first 2 years after the start of the treatment, an MRI will be made every 3–12 months. The check-ups in the hospital are 4 times a year after the starting the treatment: twice with the nurse specialist and twice with the neurologist. If the treatment is successful (no clinical or radiological disease activity), monitoring (in Isala) is performed twice a year by the neurologist and twice a year by the nurse specialist [4, 5].

The frequency of MRI monitoring is determined by the disease-modulating agent used. Furthermore, an MRI of the brain and spinal cord is required every 5 years. Blood tests are also frequently done, from once a month to every 6 months, depending on the type of DMT [4].

The MS patients come physically to the hospital and have a face-to-face consultation with their HCP.

### Intervention group: MPVC and CAU

The intervention group will use MPVC consisting of two E-health tools: 1) the MSmonitor-Plus and 2) the video calling program: Beterdichtbij [22, 23].

MSmonitor-Plus allows patients to complete questionnaires, related to MS and MS-specific quality of life. By completing these every 3 months, a schematic overview can be created of the complaints so that care and treatment can be adjusted.

Beterdichtbij is a specific, secure video calling program that is used in Isala. With Beterdichtbij physical consultations can be replaced by video calling.

Patients in the intervention group receive CAU and MPVC. For MPVC, patients complete specific questionnaires four times a year, in consultation with their HCP, and they engage in video calls with their HCP at least twice a year. The patient’s answers (responses) are graphically displayed over time and recorded in the Electronic Patient File by the HCP. These responses with observation points from the HCP (during consultation) and tests (such as an MRI) inform treatment and care.

### Control group: CAU without MPVC

In the control condition patients will have unrestricted access to CAU. Participants of the control group come to the hospital physically and have face-to-face consultations with the HCP’s, without using the MSmonitor-Plus and video calling. Medical support will be documented in the Electronic Patient File.

### Data collection methods

Concerning the intervention group, part of the data collection is embedded within MSmonitor-Plus. For the present study, additional research questionnaires are administered via the eCRF (Tables 2 and 3). Both groups, intervention and control group, fill in questionnaires in the eCRF, at baseline and every 3 months thereafter.

Participating partners/informal caregivers fill in specific validated questionnaires for partners/ informal caregivers in the eCRF at baseline and then every 6 months.

After randomization, a study number is automatically assigned to the participant (MS patient). The study numbers of the MS patients from the intervention group are also used in MSmonitor-Plus. These study numbers can be added manually in MSmonitor-Plus under the heading: ““Characteristics”“so that we keep the patient’s data together for final data collection.

The participants’ partner/informal caregiver will receive the same study number (filled manually) as his partner with MS, except for a letter P after the number (P=Partner) so that we can keep track of participants belonging together.

Parallel to the MS patient-reported data we collect in MSmonitor-Plus and in the eCRF, we will obtain objective data such as Expanded Disability Status Scale (EDSS) scores, MS relapse, Adverse Events (Side effects of the DMT, all unrelated to Multiple Sclerosis adverse events), hospitalizations (SAE) and all contact moments (MSmonitor-Plus consultations, number of physical appointments, video calls, telephone checks, check date of completed questionnaires). Every 3 months, the investigator will record these data for each MS patient in the eCRF and in the Electronic Patient File.

Confidentiality of all data is achieved through secure storage. The MS study team and the study monitor have access to the data. The static analysis will be based on a pseudo-analyzed dataset.

Ultimately, there are 18 different research (Table 4) patients: in the control group, with and without a partner/informal caregiver, patients in the intervention group, with and without a partner/informal caregiver and partners/caregivers of patients in the intervention group and control group with the corresponding type of MS.

**Table 4 Tab4:** Overview of the research groups, with type of MS (RRMS, PPMS, SPMS)

**Intervention group (IG)**	**IG-RRMS**	**IG-PPMS**	**IG-SPMS**
MS patients (without partner/informal caregiver)	X	X	X
MS patients (with partner/informal caregiver)	X	X	X
Partners/informal caregivers of MS patients	X	X	X
**Control group (CG)**	**CG-RRMS**	**CG-PPMS**	**CG-SPMS**
MS patients (without a partner/informal caregiver)	X	X	X
MS patients (with a partner/informal caregiver)	X	X	X
Partners/informal caregivers of MS patients	X	X	X

*IG* intervention group, *RRMS* relapses remitting MS, *PPMS* primary progressive MS, *SPMS* secondary progressive MS, *CG* control group

Not every patient has a partner/informal caregiver or has a partner/informal caregiver who wants to participate in this study. Therefore, there will be more patients participating than partners/informal caregivers in this study.

